**Methods:**

This project will employ an interrupted time-series design with process evaluation to assess the impact, uptake, feasibility, accessibility, cost, and sustainability of the QICs over 18 months. Thirty clinicians from across Australia will be invited to join the QICs to build their capacity in leading innovation in dementia care. Clinicians will participate in a training program and be supported to develop and implement a quality improvement project unique to their service context using plan-do-study-act cycles. Regular online meetings with their peers in the QIC will facilitate benchmarking and problem-solving. Clinicians will describe their practice via monthly checklists, and guideline adherence will be determined against a set of defined criteria. Phone interviews with up to 180 client dyads will be used to assess satisfaction with care and client outcomes. Clinician interviews and field note data will be used to explore implementation and costs. Involvement of people with dementia and carers will be embedded in the study design, conduct, and reporting, in addition to clinical and industry expertise.

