### Objectives

The primary aim of this project is to implement and sustain improvements in post-diagnosis care for people with dementia and their carers by increasing adherence to three key recommendations from the *Clinical Practice Guidelines for Dementia in Australia* [2]:People with dementia living in the community should be offered occupational therapy (reflecting evidence-based programs)People with dementia should be strongly encouraged to exerciseCarers and family of people with dementia should have access to programs that provide respite and support to optimise their ability to provide care for the person with dementia.

This will be achieved by establishing three nationwide QICs (of approximately ten health professionals and their sites each) who regularly work with people with dementia and their carers. The three guideline recommendations were chosen to be implemented because adherence to them is known to be poor. Occupational therapy intervention involving home modification, education, problem solving, and activity engagement is shown to be cost-effective [18], yet in practice occupational therapists focus on assessment at the expense of intervention [19]. People with dementia are not routinely encouraged to exercise or participate in physical activity [20] despite exercise being the most effective intervention demonstrated to delay functional decline [21]. Supporting carers of people with dementia to maintain their wellbeing and to independently problem solve and manage their own needs can reduce negative carer impacts as well as delaying functional decline and reducing the occurrence of changed behaviours in the person they care for [22, 23]. Yet these types of programs are not widely available, and carers report that they need more education, skills counselling, respite, and emotional support to help them in their caring role [24, 25]. Implementation of these guideline recommendations reflects the priorities of people with dementia and carers, who have called for improved post-diagnostic care which facilitates independence and social engagement for people with dementia and provides effective support for their carers [26]. The recommendations are low-cost, acceptable, and feasible interventions that reflect broader policies around healthy ageing [27].

The secondary aim of this project is to assess the impact of the QIC on experiences and outcomes for people with dementia and their carers.

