### Outcomes

The outcomes and measures that will be used for this study are presented in Table 3. Outcomes of interest relate to guideline adherence, implementation of the QIC methodology, service level effectiveness and harms, and client dyad outcomes.

**Table 3 Tab3:** Project outcomes

Outcome domain	Details of measurement
Guideline adherence	
Exercise guideline adherence	Full adherence when: a) Clinician checklist explicitly references a discussion about current physical activity levels, and; b) Specific needs and barriers to physical activity are identified, and; c) Treatments/strategies recommended are clinical indicated based on needs/barriers, and; d) A written treatment plan for physical activity or exercise is provided to the person with dementia
Occupational therapy guideline adherence	Full adherence when: a) Home environment assessment has occurred (where applicable), and; b) Clinician checklist explicitly references identification of primary concern/s of person with dementia and carer, and; c) A written treatment plan to address needs of person with dementia and carer or give specific advice about suitable activities (that are tailored, of interest, and match capabilities) is provided
Carer support guideline adherence	Full adherence when: a) Clinician checklist explicitly references that the needs of the carer have been discussed during the consultation, and; b) Clinician checklist explicitly references clinically indicated provision of information about programs providing respite for the carer and/or other carer support services, and; c) A written treatment plan detailing key carer concerns and strategies to manage these is provided
Implementation	
Uptake	• Exposure: the extent to which clinicians use the materials and online training course • Initial use: initial changes in adherence to guideline recommendations
Sustainability	• Continued changes in adherence to guideline recommendation.
Feasibility	• Recruitment: attraction of implementation clinicians and participating organisations • Consent rate for people with dementia and their carers agreeing to be contacted for follow-up • Maintenance: involvement in the program and contribution to data collection • Withdrawals

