#### Guideline adherence

The primary outcome of the implementation evaluation is changes in guideline adherence over time. Guideline adherence will be assessed using monthly checklists completed by implementation clinicians about their consultations with people with dementia and/or carers. Clinicians will complete the checklists for the first ten consecutive consultations each month. Clinicians will be asked to provide a ‘snapshot’ of the consultation including its purpose, content, and outcomes. A process for guideline adherence scoring was modelled on methods used in Kortekaas et al. [48] and van Fenema et al. [49]. Key indicators of guideline adherence were developed in consultation with clinical and consumer experts (see Table 3). Two independent researchers will rate whether the practice reported by the clinician was inadequately (− 1), partially (or unclear; 0), or fully adherent (+ 1) to the relevant recommendation. In cases of disagreement, a third external clinical academic will be contracted to make a final decision. A follow-up phone interview with a random selection of client dyads each month up to 5 weeks after the consultation will be used to verify these reports, and ‘agreement’ between the client dyad and clinician will be assessed. Phone interviews will be conducted by the study team with both the person with dementia and their carer where possible, or just the carer where they are directly participating as a client of clinicians in the ‘carer support’ or the person with dementia is unable to participate in a phone call. People with dementia who attend the consultation alone (including those who live in long-term care) will not be contacted by phone. Interviews will gather perspectives from the dyad or carer about their recollection of the consultation and the extent of guideline adherence from their perspective. Clinician and client dyad data will be triangulated with field notes from QIC meetings, online message board participation, and other contact with the research team.

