Feasibility data elicited from field notes and records will be provided descriptively so that it is possible to determine how many people expressed interest, how many formally participated, and how many people withdrew (and reasons for withdrawal). We will present information about the characteristics of the clinicians and their workplaces. We will also describe engagement and exposure to the intervention through presentation of time spent participating in the online training and participation in other components of the intervention such as number of contributions to the online community of practice and completion of the implementation plan. Data from the NOMAD and QIKAT tools regarding implementation readiness and proficiency will be presented descriptively (with means and standard deviations where appropriate).

The mixed sources of data will be used to explore factors underlying successful implementation. The percentage increase in average guideline adherence during the 9-month pre- and post-intervention periods will be calculated for individual clinicians, to represent implementation success. *T* or correlation tests (where appropriate) will be used to identify the impact of workplace characteristics, time engaged in the intervention, and NOMAD/QIKAT scores on implementation success. Qualitative data will be used to explore and contextualise the findings.

A cost-benefit analysis will be used for the economic evaluation [54]. The costs associated with establishing and running the QIC will be compared to the monetary benefits of implementing this strategy. The QIC will be considered value for money (i.e. cost-beneficial) if benefits exceed costs. Benefits will be considered from the perspective of implementation clinicians’ point of view. The return on investment will also be estimated as the ratio of benefits divided by total costs of the intervention (i.e. the benefit-cost ratio) [54].

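### The exploratory tests of implementation success leave out QIC membership, so a characteristic that happens to track QIC can be reported as having an impact

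*Protocol article*

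**What the plan says.** The Objectives section sets up "three nationwide QICs (of approximately ten health professionals and their sites each"), so about 30 clinicians in all. The Quantitative analysis section defines implementation success as follows: "The percentage increase in average guideline adherence during the 9-month pre- and post-intervention periods will be calculated for individual clinicians". It then names t or correlation tests, which "will be used to identify the impact of workplace characteristics, time engaged in the intervention, and NOMAD/QIKAT scores on implementation success". These tests take one predictor at a time. QIC is not named as a factor, stratum or covariate. The sentence on fitting confounders as covariates stands earlier in that section and concerns the segmented regression only.

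Elsewhere the article ties several things to the QIC:

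- **Scoring.** Each consultation is rated up to "fully adherent (+ 1) to the relevant recommendation". Table 3 lists four requirements for exercise, ending with "A written treatment plan for physical activity or exercise is provided to the person with dementia". It lists three for occupational therapy, one of them a home assessment that counts only where applicable, and three for carer support, ending with "A written treatment plan detailing key carer concerns and strategies to manage these is provided".
- **Education.** The Educate section makes the clinical content specific to one of the three topics.
- **Peers.** The Quality management section has clinicians meet and benchmark monthly within their own QIC.
- **Clients.** In the carer-support QIC the client may be the carer alone (Guideline adherence; Service and client-level outcomes).

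**The concern.** The QIC can influence the measured gain, through criteria, content and peers. It may also be related to the predictors: site types range from general practice to residential care and need not be evenly spread over three topics, and engagement or NOMAD scores may vary with the group a clinician meets. If both links are present, QIC confounds the one-predictor tests, and a workplace characteristic with no effect of its own can look like a driver because it is commoner in the QIC whose scores rose most.

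The article says it will identify which elements of the strategy contributed to adherence and that the outcomes will inform large-scale strategies. In the quantitative plan, these tests are what relates characteristics and engagement to success, so a spurious result could be carried into that advice.

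**Working it through.** **Inputs from the document.** The Abstract gives the number: "Thirty clinicians from across Australia will be invited to join the QICs". They form three QICs of about ten, with one gain per clinician. No alpha, power or effect size is given for these tests (the 83% power belongs to the monthly time series), so there is no figure of the plan to reproduce.

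**Assumed inputs.** Two-sided 5% tests; no effect of the characteristic within any QIC; mean gains and prevalence of the characteristic by QIC as stated below.

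**Tests compared.** Unadjusted: t = r·√(28/(1 − r²)), on 30 − 2 = 28 df. Adjusted: the same with both variables taken as deviations from their QIC means, t = r·√(26/(1 − r²)), on 30 − 4 = 26 df.

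**Step 1: size of a spurious difference.** Take mean gains of 5/15/25 points and prevalence of 20/50/80%.

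- With the trait: (0.2·5 + 0.5·15 + 0.8·25)/1.5 = 28.5/1.5 = 19 points.
- Without it: (0.8·5 + 0.5·15 + 0.2·25)/1.5 = 16.5/1.5 = 11 points.

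The difference is 8 points with no true effect. With gains of 10/15/20 it is 17 − 13 = 4 points.

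**Step 2: false-positive rate, unadjusted** (20,000 runs per cell; gap = lowest to highest QIC mean gain, in within-QIC SDs):

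| Prevalence by QIC | gap 0 | gap 0.5 | gap 1 | gap 2 |
|---|---|---|---|---|
| 50/50/50% | 5.1% | 5.0% | 5.2% | 5.1% |
| 30/50/70% | 4.8% | 6.6% | 9.8% | 20.6% |
| 20/50/80% | 4.8% | 8.5% | 17.1% | 41.6% |
| 10/50/90% | 5.0% | 10.4% | 27.2% | 68.1% |

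With QIC as a factor, every cell lies between 4.8% and 5.3%. A continuous predictor behaves alike: with QIC means of −0.5/0/0.5 SD the unadjusted rates are 5.0%, 6.9%, 11.3% and 26.1%.

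On a points scale with within-QIC SD 15, two separate sets of runs (6,000 and 20,000) gave:

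- gains 10/15/20, prevalence 20/50/80%: 11.4% and 10.6%;
- gains 5/15/25, same prevalence: 24.5% and 25.1%;
- gains 5/15/25, prevalence 10/50/90%: 41.2% and 42.0%.

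Adjusted rates were 5.0–5.3%.

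**Step 3: the relative reading of percentage increase.** Suppose adherence is the share of checklists fully adherent, every QIC gains 15 points, and baselines are 20/40/60%. The relative increases are 15/20 = 75%, 15/40 = 37.5% and 15/60 = 25%. With 90 checklists per clinician per period (10 × 9 months) and a between-clinician baseline SD of 5 points, the unadjusted rate is 16.1% at 30/50/70% and 33.4% at 20/50/80%. The adjusted rate is about 4%. Baselines of 20/30/40% give 10.4% and 18.5%. With the same data measured in points, the unadjusted rate is 5.0–5.2%.

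**Step 4: cost of adjusting.** With residual SD held fixed, the standard error grows by √(total trait variance / within-QIC trait variance). The total is 0.5 × 0.5 = 0.25.

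- 20/50/80%: within = (0.16 + 0.25 + 0.16)/3 = 0.19; √(0.25/0.19) = 1.15.
- 10/50/90%: within = (0.09 + 0.25 + 0.09)/3 = 0.143; √(0.25/0.143) = 1.32.

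**The case against.** The strongest reply has four parts.

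1. **The analysis is exploratory.** The paragraph is framed as exploring factors, sets no decision rule and adds qualitative data for context. This stands and limits the weight of the point. It does not cure a confounded comparison.
2. **The article condenses a fuller plan.** It does not say outright that all clinicians are pooled, and stratification could be specified elsewhere. This stands in part. But the article does name the outcome, the predictors and a family of one-predictor tests, so the point concerns a stated method and not merely missing detail.
3. **Neither condition is documented.** Nothing describes how site types fall across QICs, or shows that gains will differ. Four criteria against three does not imply different gains, and on an absolute scale constant differences in difficulty cancel in a pre-to-post change. This stands. It is why the point is conditional, and why the relative reading of the gain matters.
4. **The mechanism can be overstated.** All QICs use one checklist process, one −1/0/+1 scale and one rating procedure; only the criteria differ. Profession is not clearly among the predictors to be tested. Both stand.

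A reader might infer that characteristics tracking QIC topic will be reported as drivers, or that each QIC is measured on a different instrument. The documents support neither.

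**Conclusion.** The point holds as a conditional weakness of a secondary analysis. The one-predictor tests do not account for QIC, and the article itself makes QIC a plausible common cause of predictor and outcome. Under the assumed inputs, the false-positive rate stays near 5% if either condition fails, is roughly 7–11% when both are mild, and reaches about 40% when both are strong. The 68% corner of the grid needs an extreme combination and should not be taken as typical. Adjustment returns the rate to about 5% throughout.

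The prevalences, gains, SDs and baselines are all assumptions, because the article gives no QIC-specific figures. The size in this trial is therefore unknown until the make-up of the QICs is seen. The primary segmented regression is unaffected.

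**What to change.** Regress each clinician's gain on the characteristic with QIC as a three-level fixed factor, or use within-QIC (partial) correlations in place of simple ones. Show the unadjusted result alongside; this also keeps visible any between-QIC variation that is of interest in itself, for example in time engaged. Report the results as associations and drop the word impact. Say whether the percentage increase is in points or relative to baseline.

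The cost is a few sentences of text, two residual degrees of freedom (28 to 26) and a loss of precision. Where a characteristic tracks QIC, the standard error widens by about 15% (20/50/80% split) to 32% (10/50/90% split). With about ten clinicians per QIC, a characteristic that nearly coincides with QIC cannot be separated from it, and the report should say so.

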Quality improvement collaboratives have been successfully implemented to increase rates of breast feeding [14] and organ donation [15], reduce central line-associated bloodstream infection [16], and decrease post-stroke length of stay [17]. To our knowledge, QICs have not yet been used as an implementation strategy in community-based dementia care. Whether they are an accessible, feasible, cost-effective, and sustainable method of improving guideline adherence in dementia care is not known.

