## Methods

### Design

An overview of the project per guidelines by Proctor et al. [28] appears in Table 1. The impact of QICs on guideline implementation and outcomes for people with dementia and carers (‘client dyads’) will be evaluated in this implementation research project using an interrupted time-series design [29]. Interrupted time series is a strong evaluative design for estimating the impact of an intervention in non-randomised settings because it allows for detailed assessment of longitudinal trends associated with an intervention [30]. Feasibility, acceptability, cost-effectiveness, and sustainability of the model will be evaluated using an inbuilt mixed-methods process evaluation [31]. Both administrative data and data collected from participating health professionals, their employing organisations, and their clients with dementia and carers will inform the outcomes for this study.

**Table 1 Tab1:** Overview of project per guidelines by Proctor et al. [28]

Action	Description
Name it	Establishment of QICs to improve care for people with dementia and their carers
Define it	QICs enable rapid, sustainable improvements in care by bringing together health services to learn together, share ideas, and benchmark outcomes
Specify it	
a) The actor	The project team establishes and supports the QICs; Implementation clinicians form the QICs and conduct quality improvement (using PDSA cycles)
b) The action	Completion of an online training course, development of a site-specific implementation plan, and enactment of this plan (using PDSA cycles)
c) Action target	“Implementation clinicians”: health professionals across Australia who have some leadership responsibilities yet are still closely connected to the delivery of services and can introduce changes to practice
d) Temporality	The clinicians will participate in online training, develop a sites-specific implementation plan, and then enact the plan.
e) Dose	Seven education modules of 2 hours each, to be completed over 8 weeks; 11 virtual QIC meetings
f) Implementation outcome affected	Primary outcome: adherence to recommendation as described in the criteria in Table 3.
g) Justification	The intervention was designed to match with factors known to enable evidence-based care for people with dementia and their carers and to be relatively ‘light touch’ and promote rapid change

*Abbreviations*: *PDSA* plan-study-do-act, *QIC* quality improvement collaborative

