Costs associated with establishing and running the QIC will be estimated. Total costs include costs of providing the intervention (personnel, technology, stipends, and development and distribution of educational materials) and in-kind contribution required for each site estimated using a ‘bottom-up’ micro-costing approach. Costs will be estimated using administrative data and resource use questionnaires administered to key implementation site personnel. The monetary benefits of adopting and implementing the QIC, from implementation clinicians’ point of view, will be determined using contingent valuation techniques [53]. This technique allows for a monetary value to be placed on a good or service that is not yet available in the marketplace. The maximum amount of money that implementation clinicians would be willing to pay for the perceived benefits (buying price) of implementing the QIC will be estimated using their responses to a willingness to pay (WTP) questionnaire. As per best practice guidelines [53, 54], the WTP questionnaire will (a) identify the benefits that are likely to be realised from the QIC, (b) assess prior knowledge about QIC and attitudes toward it, and (c) establish respondents’ WTP.

Finally, implementation clinicians and managers will complete an organisational network map of their implementation site to describe the structure of their services, relationships between staff members, and potential sources and supporters of innovation. These maps can be used to examine the complex interactions between structures and people that might not be captured in an interview [55]. Maps will also be used to examine the penetration of the project in terms of the variety of sites, funding models, professional backgrounds, level of seniority, and types of roles engaged with the QICs. Clinician checklists, interviews, client dyad phone calls, and field notes will be examined to assess whether participation improved the reach of services to previously underserviced clients.

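### The value-for-money verdict sets clinicians' stated willingness to pay against cost, with no measured outcome in it, and the cost-effectiveness named under Design has no analysis

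*Protocol article*

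**What the plan says.** All places are in the protocol article.

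- **Quantitative analysis** names the method, "A cost-benefit analysis will be used for the economic evaluation", and the decision rule, "The QIC will be considered value for money (i.e. cost-beneficial) if benefits exceed costs". It fixes the viewpoint, "Benefits will be considered from the perspective of implementation clinicians’ point of view", and adds a benefit-cost ratio as the return on investment.
- **Process evaluation** defines the benefit figure: "The maximum amount of money that implementation clinicians would be willing to pay for the perceived benefits (buying price) of implementing the QIC" is to be estimated from a questionnaire. One task of that questionnaire is to "identify the benefits that are likely to be realised from the QIC". Costs are built bottom-up from delivery of the programme and each site's in-kind contribution.
- **Design** states: "Feasibility, acceptability, cost-effectiveness, and sustainability of the model will be evaluated using an inbuilt mixed-methods process evaluation".
- **Background** describes the gap in knowledge: "Whether they are an accessible, feasible, cost-effective, and sustainable method of improving guideline adherence in dementia care is not known".
- **Objectives** poses the economic research question as return on investment, glossed as cost-benefit.

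**The concern.** The study measures whether adherence changes and how clients and carers fare. The verdict on whether the collaboratives were worth their cost draws on none of these measurements. It rests on how highly the people who took part value taking part. An unqualified statement of value for money could therefore be published next to a null adherence result. The reverse is also possible: a programme that helped clients and carers could be called poor value because clinicians did not put a price on that help.

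The Discussion expects the outcomes to inform large-scale strategies. Someone deciding whether to fund such a programme would probably read a value-for-money statement as saying that the money bought better care, and the rule does not establish that. The Design section strengthens that reading by listing cost-effectiveness among the things to be evaluated.

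**Working it through.** The documents state no cost, willingness-to-pay value, threshold or benefit-cost ratio, so there is no figure to reproduce. The check traces what goes into the rule and sets the relevant sections side by side.

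**1. Inputs to the rule**

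| Quantity | Where defined | Enters the verdict? |
|---|---|---|
| Clinicians' stated willingness to pay for perceived benefits | Process evaluation | Yes, as benefits |
| Delivery cost plus in-kind site contribution | Process evaluation; Table 3 | Yes, as costs |
| Guideline adherence (primary outcome) | Guideline adherence; Table 3 | No |
| Client and carer satisfaction | Service and client-level outcomes | No |
| DEMQOL-Proxy, Zarit burden | Service and client-level outcomes | No |
| Segmented-regression result | Quantitative analysis | No, and the verdict is not conditional on it |

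**2. The rule as a formula**

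Let W be a clinician's stated willingness to pay, n the number of clinicians and C the total cost. Summing W over clinicians is my assumption, because the article does not say how answers are aggregated. Then

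benefit-cost ratio = n × mean(W) / C, and the verdict is favourable if this exceeds 1.

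For illustration, take n = 30 (the planned number of clinicians) and assumed total costs:

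- C = $100,000: break-even mean W = 100,000 / 30 ≈ $3,333
- C = $300,000: 300,000 / 30 = $10,000
- C = $600,000: 600,000 / 30 = $20,000

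At C = $300,000, a mean W of $15,000 gives 30 × 15,000 / 300,000 = 1.5 (favourable). A mean W of $5,000 gives 30 × 5,000 / 300,000 = 0.5 (unfavourable). Each result is the same for an adherence change of 0 or of 15 points. This is true by construction once W and C are held fixed. It shows which quantities the formula contains. It does not show that W would fail to respond to a real change in adherence.

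**3. Can perception carry the outcome into the verdict?**

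Partly. Table 2 and Quality management provide for audit and feedback from clinician and dyad reports, so clinicians may have some idea of whether their practice changed. Three features weaken that link:

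- The questionnaire is framed around expected benefits, and its timing is not stated.
- The respondents also receive training, webinars, gift cards and a conference stipend of up to $1000 (Table 2; Finance), which they may value whether or not care changes.
- The Discussion expects opt-in recruitment to yield unusually engaged clinicians.

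Benefit to clients and carers counts only as far as clinicians price it. For self-reported adherence, the Discussion plans triangulation with client calls. No similar check is described for the economic verdict.

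**4. Cost-effectiveness, section by section**

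- Background: whether collaboratives are a cost-effective way to improve adherence is unknown. This is a gap statement.
- Design: cost-effectiveness of the model will be evaluated. This is a commitment, not tied to adherence.
- Abstract: cost only.
- Objectives: return on investment (cost-benefit).
- Table 3 and Process evaluation: costs and willingness to pay.
- Quantitative analysis: cost-benefit analysis and benefit-cost ratio.

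No section relates cost to a unit of adherence or of client outcome. The word used under Design therefore has no matching analysis.

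**5. What an outcome-based summary would do**

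Take C divided by the gain in adherence. With the assumed C = $300,000 and a gain of 15 points (the minimum change in the sample-size paragraph, read here as percentage points), it is 300,000 / 15 = $20,000 per point. At half that gain it is 300,000 / 7.5 = $40,000 per point. At zero gain there is no finite ratio. Unlike the benefit-cost ratio, this figure moves directly with the measured result.

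**The case against.** The strongest reply is that the protocol answers the question it asks. The research question is return on investment, glossed as cost-benefit, and the planned analysis delivers that. Contingent valuation is a recognised way to put a money value on benefits, and perceived value is what it is meant to capture. The clinician perspective is declared openly, twice. From that perspective, training and peer contact are legitimate benefits, and stipends and materials are counted as costs. Choosing cost per outcome instead would be a preference between accepted methods.

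Much of this stands. Using willingness to pay is not an error, and the cost-benefit analysis should stay. Three stronger readings are tempting, and the documents do not support them:

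- **That the protocol promises the cost-effectiveness of improving adherence and then omits it.** The link to adherence appears only in the Background, as a gap in knowledge. The commitment under Design concerns the model, and the research question asks for cost-benefit. What remains is a mismatch of terms.
- **That the verdict is shown to be blind to adherence.** An unchanged verdict for unchanged willingness to pay is a tautology. Audit and feedback leave an indirect route through perception.
- **That comparing benefits with costs without an interval is itself a fault with a calculable error rate.** An article may leave methods for uncertainty to the full plan, and any such rate would rest on a spread of willingness to pay that the documents do not give.

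The reply does not cover the label. The clinician perspective is declared for the benefits, but the verdict is attached to the collaborative without that qualifier and without reference to the adherence result. The article itself states the rule, the perspective and the benefit source, so this is not a detail left to an unseen plan.

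**Conclusion.** The concern holds in a limited form. The verdict is clinicians' perceived value against cost. Measured adherence and client outcomes neither enter nor condition it except through what clinicians perceive, and it can mislead in either direction. Separately, Design names cost-effectiveness while the listed analyses provide only cost-benefit.

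The size cannot be put in figures, because the documents give no cost or willingness-to-pay values; the dollar amounts in the working are assumed. The conclusion rests on reading the benefit and cost definitions under Process evaluation and Quantitative analysis as complete. The primary analysis, the sample size and the participants are unaffected. What changes is what the trial may conclude about value, so the change is worth making but not critical.

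**What to change.** 1. **Quantitative analysis, economic paragraph.** Keep the cost-benefit analysis and the benefit-cost ratio. State the result as value from the implementation clinicians' perspective, that is, perceived value against cost. Report it beside the primary adherence result, and do not use an unqualified value-for-money label if adherence does not improve.
2. **Either add an incremental summary or correct the term.**
   - Add total cost of the collaboratives per unit (or percentage-point) gain in adherence. Take the gain from the segmented model's absolute difference from the counterfactual, and carry its uncertainty through. Where the gain is near zero the ratio is unstable, so show cost and gain separately as well.
   - If that summary is not wanted, replace cost-effectiveness under Design with cost-benefit from the clinicians' perspective.

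Cost per additional fully adherent consultation is not a suitable unit. Adherence is scored −1, 0 or +1 on at most ten consultations per clinician each month, and total consultation volume is not a listed data item. Nor is a requirement of statistical significance needed before the economic result is reported.

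The cost is some rewording and one small calculation on cost and adherence data already being collected. The downside is a possibly less favourable economic conclusion.
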